#### **3.3. Rationale of study design**

Although WHO recommends Ambisome® 40 mg/kg for HIV VL co-infected patients, this is based on limited information from Mediterranean countries; there are no data available from Ethiopia and there is little information available on the efficacy of the test treatments and no established standard treatment with a proven efficacy (of at least 90%) in East Africa. It is therefore not possible to design a comparative study as there is insufficient data to set margins for superiority or non-inferiority. The design of the study will therefore focus on establishing efficacy of two potential test treatments for VL in HIV co-infected individuals.

Recent practice by MSF in their treatment centre at Abdurafi using Ambisome® 30 mg/kg demonstrated a cure rate of only 74% in primary VL cases and of 38% in relapse cases. Increasing the dose to 40 mg/kg seems reasonable to achieve better cure rates. There are no other realistic options for monotherapy with the drugs that are currently available. SSG is too toxic and miltefosine while better tolerated is less effective than SSG as monotherapy.

Combination regimens are attractive as they offer potential added effects; preliminary experience from MSF using Ambisome® 30 mg/kg with miltefosine for 28 days increases the initial cure rate in relapse cases to 87%, while in primary VL this remains at 74%. Moreover, the combination seems to be well tolerated. This study aims to identify a treatment regimen is safe and effective for all HIV VL co-infected patients in both primary and relapse cases. While including primary and relapse cases makes the study population more heterogeneous, the outcome of the trial could be applicable to all cases that present. In the final analysis, cure rates for both arms will be stratified in both arms to see differences between primary cases and

relapses. The study will not be powered to detect statistically different differences as for this the sample size would have to be unrealistically much larger.

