#### **10.9. Interim analysis**

There will be sequential analysis every 20 patients (10 patients in each arm), up to completion of the study. A maximum of 7 analysis will be performed. DSMB will consider if both treatment arms should be continued based on pre-defined criteria set in the sequential analysis. DSMB will also review the available safety data (AEs, SAEs) for both treatment arms.

In order for the findings of this study to be generalizable the population included in this study is heterogeneous (i.e. includes relapse and primary VL patients, patients currently on ART and those that will start ART). In order to address potential concerns regarding the heterogeneity of the population and reduce the likelihood of rejecting a treatment that may be effective in a sub section of the population a test to assess heterogeneity will be performed when a treatment is stopped. This test will be

conducted to verify on the available data if there is a signal of interaction ( $p < 0.10$  = possible interaction) between strata (primary VL or relapse; patients currently on ART or patients initiated on ART during the study) and treatment (magnitude of the treatment effect is dependent upon strata). In absence of signal of interaction ( $p > 0.10$ ) the magnitude of the difference in success rates between treatments should be relatively homogeneous across strata. In presence of significant signal interaction, the treatment effect will have to be adjusted on strata to know whether both therapeutic strategies have the same success rate. Depending on the outcome of this test for heterogeneity, recruitment may be continued into one stratum. This decision will be taken by the sponsor following consultation with the DSMB and other relevant authorities.

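### Section 10.9 reads a non-significant interaction test as homogeneity across strata, but when the first arm stops the trial is too small for that test to show it

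*Protocol*

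**What the plan says.** Protocol Section 10.9 provides that "a test to assess heterogeneity will be performed when a treatment is stopped". The strata are primary versus relapse VL, and already on ART versus starting ART during the study. The stated aim is to "reduce the likelihood of rejecting a treatment that may be effective in a sub section of the population". A p-value below 0.10 is called a possible interaction. Above 0.10, "the magnitude of the difference in success rates between treatments should be relatively homogeneous across strata". The section adds: "Depending on the outcome of this test for heterogeneity, recruitment may be continued into one stratum", and gives that decision to the sponsor after consulting the DSMB and other authorities. Looks take place after every 10 patients per arm.

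Section 3.3, on primary versus relapse cases, concedes: "The study will not be powered to detect statistically different differences". It also cites programme cure rates. AmBisome 30 mg/kg alone cured 74% of primary and 38% of relapse cases. Adding miltefosine "increases the initial cure rate in relapse cases to 87%, while in primary VL this remains at 74" (per cent).

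**The concern.** A p-value above 0.10 shows only that the data did not rule out equal effects. It supports homogeneity only if the study would probably have detected a difference that matters, or if a confidence interval excludes one. Section 10.9 gives no power for the test, no smallest interaction of interest and no interval.

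The costly error here is a missed interaction. If an arm crosses the lower boundary because it fails in one stratum while working in the other, this step is the safeguard. Under the present wording a missed interaction reaches the sponsor and the DSMB as reassurance that the strata behave alike. The figures in Section 3.3 make a large interaction plausible.

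**Working it through.** **1. Reproducing the plan's own figure.** Inputs from the Synopsis (Statistics) and Section 10.1: p0 = 0.75, pa = 0.90, alpha = beta = 0.05, looks every 10 patients.

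- theta = ln[0.90 × 0.25 / (0.75 × 0.10)] = ln 3 = 1.0986
- a = (2/theta) × ln(1/(2 × 0.05)) = 4.192; c = theta/4 = 0.2747
- V per look = 10 × 0.75 × 0.25 = 1.875; correction for discrete looks: a' = 4.192 − 0.583 × √1.875 = 3.394
- Maximum n = a'/(c × 0.1875) = 65.9

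This matches the stated maximum of 66 per arm, so the rebuilt boundaries are a fair basis for stopping sizes.

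**2. Size of the interaction.** Section 3.3 gives a treatment difference of 74 − 74 = 0 points in primary cases and 87 − 38 = 49 points in relapse cases, so an interaction of 49 points. The background in Section 1 instead gives about 80% for the combination in both groups. That implies (80 − 38) − (80 − 74) = 36 points. Smaller interactions were also examined. The primary share is assumed to be 0.5 to 0.7; the earlier programme in the Synopsis had 116/195 = 0.59.

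**3. Miss rate (p > 0.10) when the first arm stops.** Both arms were simulated through the boundaries and the interaction tested at the first stop. Cure rates are primary/relapse, monotherapy v combination.

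| Assumed cure rates (%) | Interaction (points) | Mean n per arm at first stop | Missed, likelihood-ratio test |
|---|---|---|---|
| 74/38 v 74/87 | 49 | 16–18 | 53–55% |
| 74/45 v 74/85 | 40 | 17–19 | 61–62% |
| 75/55 v 75/85 | 30 | 19–21 | 68–70% |
| 75/65 v 75/85 | 20 | 22–23 | 75–77% |
| 90/60 v 90/90 | 30 | 27–31 | 66–69% |

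A Wald test on the log odds ratio (0.5 correction) misses more: about 69% for 49 points and 80 to 84% for 25 to 30 points. The 25-point case is 74/62 v 74/87. A recheck agreed at primary shares of 0.5 to 0.6 and gave figures a few points higher at 0.7.

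At 10 to 20 per arm with no interaction, the likelihood-ratio test rejects about 14 to 18% of the time and the log-odds Wald test about 4 to 8%, against a nominal 10%. The first therefore understates misses and the second overstates them.

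**4. Where the problem eases.** For 49 points at fixed n with 60% primary, the miss rate over three tests (the two above and a risk-difference z test) is 43–58% at 20 per arm, 30–43% at 30 and 20–30% at 40. For 30 points (75/55 v 75/85) it is 68–80%, 61–71% and 55–63%, and still 42–48% at 60 per arm.

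**5. Precision of the interaction estimate.** The four binomial variances are 0.74 × 0.26 = 0.1924 (twice), 0.38 × 0.62 = 0.2356 and 0.87 × 0.13 = 0.1131. With 60% primary, the standard error at n per arm is √[0.3848/(0.6n) + 0.3487/(0.4n)].

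- n = 20: 0.275; 90% half-width 1.645 × 0.275 = 45 points
- n = 30: 0.225; 37 points
- n = 40: 0.194; 32 points
- n = 66: 0.151; 25 points

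**6. Size needed.** For 80% power at two-sided 0.10, n per arm = (1.645 + 0.842)² × (0.3848/0.6 + 0.3487/0.4) / 0.49² = 39 for 49 points. The same method, with the table's rates, gives 62 for 40 points, 108 for 30 (75/55 v 75/85) and 234 for 20. Only the first two lie within the maximum of 66.

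**The case against.** The strongest reply is that Section 10.9 decides little by itself. The triangular boundary stops the arm, not this test. Continuing in one stratum is permissive and rests with the sponsor after consultation. A reader might infer that p > 0.10 automatically closes the arm for every patient; the text does not say so. The wording is also cautious, 0.10 is a lenient threshold, and Section 3.3 discloses the lack of power. All of this stands. It limits the consequence but does not repair the inference, which is the one reading of p > 0.10 that the decision-makers are given.

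The numbers are conditional. The protocol does not define a clinically important interaction, the 38% comes from 30 mg/kg while the trial arm is 40 mg/kg, and the stratum split is assumed. A risk-difference z test misses less often (43% at a fixed 20 per arm for 49 points). A reader might also infer that the test misses most large interactions at any size. That is not so for 49 points once both arms reach about 30.

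Sections 3.3 and 10.6 plan comparisons of primary and relapse cases and leave detail to the SAP. Section 10.6 times them at the final sequential analysis and after one year, so they do not cover an early arm stop.

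Finally, the argument about losing an effective regimen applies to lower-boundary stops; after an upper-boundary stop nothing is being discarded. The primary single-arm decision and its error rates are unaffected.

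**Conclusion.** The point holds as a faulty inference that the protocol itself states, not as a missing detail. At the sizes where the first arm stops in the main scenarios (about 16 to 22 per arm), a likelihood-ratio or log-odds Wald test at 0.10 misses an interaction of 25 to 49 points roughly 53 to 84% of the time. Where cure rates are higher and the first stop comes at about 27 to 31 per arm, a 30-point interaction is still missed about two times in three by the likelihood-ratio test. These figures rest on proxy stratum rates and a primary share of 0.5 to 0.7. A non-significant result there cannot support homogeneity, and this undercuts the step's stated purpose when an arm stops for inadequate efficacy. The ART strata face the same difficulty; their split is not given, so no figure is offered. The documents do not support saying that the rule itself closes an arm. The change is worth making, but the primary analysis does not depend on it.

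**What to change.** In Section 10.9, replace the sentence on p > 0.10 with a statement that such a result is inconclusive and is not evidence of homogeneity. At each arm stop, give the DSMB and the sponsor:

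- cure rates by stratum (primary/relapse, and ART status) in each arm, with exact confidence intervals;
- the interaction estimate with its 90% confidence interval.

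Base the discussion of continuing in one stratum on these, not on the p-value alone. A fixed homogeneity margin of, say, 20 points is not advised: the 90% half-width is about 25 points even at 66 per arm at the cited rates, so the margin could hardly ever be met.

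The cost is a wording change and one extra table per stopped arm, from data already collected. Boundaries, sample size and treatment are untouched. The drawback is that the sponsor will rarely be able to claim homogeneity.

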| 
Statistics
 
Summary of analysis
 | 
Primary Endpoint Analysis: Day 29
 
The study is designed and will be analysed according to group-sequential methods, specifically the triangular test. The triangular test is one way of analysing group sequential trials and uses straight line stopping boundaries. It involves analysing the data as they accumulate, with points being plotted relative to a triangular region and stopping when the upper or lower boundary of the region is crossed (Graph 1). It has the advantage over other methods of analysing group sequential trials, such as the discrete sequential probability ratio test, in that a closed continuation region is used ensuring that the trial stops within a pre-specified maximum sample size.
 
The type I error rate and power of the study were set to 5% and 95%, respectively (<math>\alpha=0.05</math>, <math>\beta=0.05</math>) with parameters <math>p_0=0.75</math> and <math>p_a=0.90</math>. Based on these specifications, the boundaries of the test were calculated for the null hypothesis, <math>H_0: p \leq p_0</math>, and the alternative hypothesis, <math>H_a: p > p_0</math> (see Graph 1). Based on the rationale above, rejecting the null hypothesis, <math>H_0: p \leq p_0</math>, (crossing the upper boundary) means that we can consider the regimen for compassionate use while failing to reject the null hypothesis (crossing the lower boundary) means that we cannot consider the regimen for compassionate use. Data from each arm will be analysed (for the evaluable patient population or per protocol analysis) after every 10 patients reach the primary endpoint of initial cure, where the actual values of Z and V will be calculated and then plotted on the graph. Depending on where the point falls, that arm of the trial will either continue collecting data for another 10 patients or will stop, concluding with a rejection of the null hypothesis (adequate efficacy) or a non-rejection of the null hypothesis (inadequate efficacy). In the final analysis, asymptotic properties will be used to calculate unbiased estimators of the response rate and its 95% confidence interval taking into account the sequential nature of the analyses.
 
Secondary Endpoint Analysis:
 
When the analyses concludes that an arm should be stopped (i.e. a boundary has been crossed), survival at 1 year will also be evaluated. Due to sequential design employed and the different treatment options to be determined by day 29 outcomes (i.e. repeat treatment and/or pentamidine prophylaxis), subsequent analyses (i.e. the secondary endpoint) are likely to be descriptive only. Such descriptive analyses will focus on survival (alive and disease-free) at 12 months post day 29 assessment and relapses between day 29 and 12 months follow-up, by arm and day 29 outcome.
 
Safety Analysis
 
Adverse events (AEs) will be described on treatment and during follow-up. AEs will be coded using MedDRA and tabulated by severity / CTC V4 AE grading. Causality of AEs will also be tabulated. Serious Adverse Events (SAEs) will be described by individual narratives based on the SAE reports provided by the site investigators. Summary statistics will be tabulated for haematological and biochemical parameters as well as for ART efficacy (CD4 count, viral load) at each time point.
 |

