## 10. Data Analysis and Statistical Methods

### 10.1. Sample size determination

The sample size will be determined according to the sequential design for the primary outcome to be measured at day 29.

Since we are using a sequential approach, the sample size is not defined or known in advance. The maximum sample size needed per arm would be 66 patients (132 total patients) and the maximum analyses performed would be 7 (see Graph 1, upper horizontal axis). The actual sample size may be less than this, with its value depending on the value of the proportion cured.

Graph 1: Triangular region for study arms showing the boundaries for analysing the sequential trial using the Triangular Test, with the following parameters ( $p_0 = 0.75$ ,  $p_a = 0.9$ ,  $\alpha = 0.05$ ,  $\beta = 0.05$  and  $n = 10$ ).

[figure not shown]

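### Once an interaction is signalled, Section 10.9 judges whether the regimens have equal success from a strata-adjusted effect, where stratum-specific differences are needed

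*Protocol*

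**What the plan says.** Section 10.9 of the Protocol states that "a test to assess heterogeneity will be performed when a treatment is stopped". The threshold of p < 0.10 is described as a "possible interaction) between strata (primary VL or relapse; patients currently on ART or patients initiated on ART during the study) and treatment", and the section explains interaction as a treatment effect whose size depends on the stratum.

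Two branches follow:
- Without a signal, the section remarks that the difference between arms should be fairly uniform across strata. It orders no analysis.
- With a signal, it says that "the treatment effect will have to be adjusted on strata to know whether both therapeutic strategies have the same success rate".

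It then adds that recruitment might go on in a single stratum, depending on the heterogeneity test. The section's declared aim is to avoid rejecting a regimen that works in part of the population.

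Section 3.3 gives the prior experience behind the worry about mixed populations. AmBisome 30 mg/kg alone "demonstrated a cure rate of only 74% in primary VL cases and of 38% in relapse cases"; adding miltefosine "increases the initial cure rate in relapse cases to 87%, while in primary VL this remains at 74" per cent.

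**The concern.** If the effect depends on stratum, there is no single treatment effect to adjust. A strata-adjusted estimate is then a weighted average of unequal differences, and two things follow.

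- Its value depends on how many primary and relapse patients happened to be recruited. Randomisation is stratified by this factor, but its proportions are not fixed.
- An effect present in only one stratum is averaged with the absence of effect in the other.

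The sentence therefore works against the section's own aim. It applies just when the data have indicated that one stratum may respond differently, and it answers with a summary that blurs that stratum. What is at stake is the statement on whether the two regimens perform alike, made when an arm stops.

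This is not detail left to the SAP. It is a rule the Protocol states, and an SAP that follows the Protocol would inherit it.

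**Working it through.** **1. The plan's own figure.** Section 10.1 states: "The maximum sample size needed per arm would be 66 patients (132 total patients) and the maximum analyses performed would be 7". The inputs are p0 = 0.75, pa = 0.90, alpha = beta = 0.05 and groups of 10 per arm.
- θ = ln[0.90 × 0.25 / (0.75 × 0.10)] = ln 3 = 1.0986
- a = (2/θ) ln(1/(2 × 0.05)) = 4.192; c = θ/4 = 0.2747
- Information per look = 10 × 0.75 × 0.25 = 1.875; correction for discrete looks = 0.583 × √1.875 = 0.798
- Vmax = (4.192 − 0.798)/0.2747 = 12.36; N = 12.36/0.1875 = 65.9, so 66 per arm and 7 looks

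The figure reproduces and is not in dispute. It sets the range of sizes at which an arm can stop. Looks fall every 10 per arm, so 20, 30 or 40 per arm are realistic as well as 66.

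**2. What the adjusted effect averages.** Assumed rates, from Section 3.3: primary 74% v 74% (difference 0), relapse 38% v 87% (difference 49 points). With equal allocation within strata, the Mantel-Haenszel weights equal the stratum shares. At 66 per arm:

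| Primary:relapse per arm | Average difference | Adjusted test significant |
|---|---|---|
| 44:22 | 22/66 × 49 = 16.3 points | 55% |
| 33:33 | 33/66 × 49 = 24.5 points | 88% |
| 22:44 | 44/66 × 49 = 32.7 points | 99% |

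The true stratum rates are the same in every row; only the case mix differs. The last column is simulated (200,000 trials per row, Cochran-Mantel-Haenszel test at two-sided 0.05, not conditioned on a signal).

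**3. Loss from averaging.** Same rates, equal strata, among trials with interaction p < 0.10 on the risk-difference scale. The comparator is a separate test in each stratum at 0.025.

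| Per arm | Adjusted test | Stratum-specific tests | Gap |
|---|---|---|---|
| 20 | 37% | 81% | 44 points |
| 30 | 54% | 87% | 33 points |
| 40 | 67% | 95% | 28 points |
| 66 | 88% | 99% | 11 points |

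With 10 patients per cell (the first row), the stratum-specific figure varies between runs from about 74% to 82%, because the tests are discrete. Without conditioning on a signal, the gaps are about 19 to 22 points at 20 to 40 per arm and 11 at 66.

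**4. Extreme case, assumed rates.** Take 90% v 65% in one stratum and 65% v 90% in the other, with 33 + 33 per arm. The average difference is 0.5 × 25 − 0.5 × 25 = 0. An interaction (log-odds scale) is signalled in 97% of trials and the adjusted test is non-significant in 96% of those, so 0.97 × 0.96 = 93% of all trials find an interaction and then fail to find a difference. The adjusted test rejects in about 4%. A 2-df joint test of no difference in either stratum rejects in 91%.

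**The case against.** Several counter-arguments have force.

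- **No test is named.** Adjusting on strata could loosely cover a model with an interaction term, and the singular noun is thin evidence for one number. This stands as a limit: the figures assume Mantel-Haenszel. The sentence still asks one yes/no question of one effect. Strictly, the Mantel-Haenszel null is no effect in any stratum, but the statistic has almost no power when the weighted average is zero.
- **Stratum results appear elsewhere.** Section 3.3 promises cure rates by primary and relapse status, and Section 10.6 announces further analyses of these groups and of ART exposure. Those belong to the final or one-year analysis, so the results would not be hidden, but the rule applied when an arm stops is unchanged.
- **The rates are borrowed.** The 74% and 38% are for AmBisome 30 mg/kg alone, whereas the trial's monotherapy arm is 40 mg/kg (Section 7.2), for which no Ethiopian rates exist. This stands: the figures illustrate and do not predict.

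Three stronger readings are tempting but unsupported:

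- A reader might infer that the two branches have been swapped. They have not, because no analysis is ordered without a signal.
- A reader might infer that the rule will call the regimens alike although they differ in every stratum. That needs opposite effects that nearly cancel. The prior data show no primary difference and a gain in relapse. Effects in one direction are still found (90% v 80% with 85% v 40%: 97% detection).
- A reader might infer that the sentence decides which arm or stratum continues. Arm stopping rests on each arm's own test against 0.75, and continued recruitment on the heterogeneity test.

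**Conclusion.** The concern holds as a flaw in how the arms are to be compared after an interaction signal. On the ordinary reading, the prescribed summary depends on case mix and dilutes an effect confined to one stratum. Under the assumed rates the cost in detection, given a signal, runs from about 44 points at 20 per arm to 11 at 66. Case mix alone moves the adjusted test from 55% to 99% at 66 per arm.

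These sizes rest on Mantel-Haenszel as the adjusted test, on prior rates that are not those of the 40 mg/kg arm, and, in the detection comparison, on equal strata. Complete cancellation is possible but the prior data do not suggest it.

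The trial's sequential design and error rates are untouched, and Section 3.3 disclaims a formal comparison of arms. Priority is therefore minor to moderate.

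**What to change.** Replace the sentence in Section 10.9 with:

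> If p < 0.10, each arm's cure rate and the between-arm difference will be reported separately by stratum with confidence intervals, and a single strata-adjusted effect will not be used to judge whether the regimens have the same success rate.

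If a strata-adjusted difference is wanted, it belongs in the case without an interaction signal. Adding one there is optional and not part of this repair.

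The cost is one sentence, carried into the SAP, with no extra patients or data. The drawback is that stratum-specific intervals will be wide: with equal strata there are only 10 to 33 patients per arm and stratum at 20 to 66 per arm. That width reflects the real uncertainty, which an averaged p-value would conceal.
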